## Abstract

**Background:**

According to current evidence and psychological theorizing proper information giving seems to be a promising way to reduce patient anxiety. In the case of surgical patients, admission to the intensive care unit (ICU) is strongly associated with uncertainty, unpredictability and anxiety for the patient. Thus, ICU specific information could have a high clinical impact. This study investigates the potential benefits of a specifically designed ICU-related information program for patients who undergo elective cardiac, abdominal or thoracic surgery and are scheduled for ICU stay.

**Methods/Design:**

The trial is designed as a prospective randomized controlled trial including an intervention and a control group. The control group receives the standard preparation currently conducted by surgeons and anesthetists. The intervention group additionally receives a standardized information program with specific procedural, sensory and coping information about the ICU.

A measurable clinical relevant difference regarding anxiety will be expected after discharge from ICU. Power calculation (α = 0.05; β = 0.20; Δ = 8.50 score points) resulted in a required sample size of N = 120 cardiac surgical patients (n = 60 vs. n = 60). Furthermore, N = 20 abdominal or thoracic surgical patients will be recruited (n = 10 vs. n = 10) to gain insight to a possible generalization to other patient groups.

Additionally the moderating effect of specific patient attributes (need for cognition, high trait anxiety) will be investigated to identify certain patient groups which benefit most.

**Discussion:**

The proposed study promises to strengthen evidence on effects of a specific, concise information program that addresses the information needs of patients scheduled for ICU stay.

## Background

Technological advances during the last decades in intensive care medicine made it possible to treat an increasing number of high risk surgical patients. Nevertheless, many patients awaiting elective surgery experience diffuse anxiety and a lack of subjective predictability regarding their stay on the intensive care unit. The psychological elements that become salient in the perioperative situation can be characterized as loss of control, irritation and uncertainty. These psychological elements are also known for contributing to postoperative complications such as delayed wound healing and an increased intake of sedatives and analgesics [1]. In addition, the strange and unfamiliar situation on the ICU in combination with sleep deprivation and ICU-noises is closely related with the incidence of a postoperative delirium also called ICU-Syndrome [2,3]. In a preliminary study it was shown that only 16% of the asked patients felt sufficiently informed and prepared for their ICU-stay [4].

According to the psychological theory of control proper preoperative information giving seems a promising way to reduce ICU-related anxiety [5-7].

A proper information program would inform the patient about the aims, prospects and the specific elements of the scheduled ICU stay. Thus, the patient learns that he/she is about to undergo a time-limited episode and that all is done in the best of his/her interest. This information together with learning about ways how to communicate in the case of specific needs gives the patient back a sense of control in this communicative difficult situation on the ICU.

A number of studies indicate that surgical patients profit from preoperative information with regard to various outcomes such as anxiety, pain and length of stay [8-17]. Nevertheless, the evidence that information regarding ICU-specific issues is beneficial is scarce [18-20] and a recent review concludes that randomised studies in this area are called for [18].

Therefore the aim of our study is to investigate the benefits of a standardized information program that prepared the patient for a scheduled ICU stay following an operation. This information program is tested in a randomized controlled trial, in which the control group receives the standard preoperative information and the intervention group the standard preoperative information plus the ICU-specific information.

The hypothesis of our study is straightforward: The information program reduces the experience of anxiety and other unpleasant emotions and cognitions that are related to the ICU stay. Furthermore we expect that the information program has a positive influence on quality of life and satisfaction with the hospital 3 months postoperatively.

## Methods/Design

This trial is based on a non-blinded, randomized controlled study design. The control group receives the routine treatment and information by the surgeon and the anesthetist, the experimental group additionally receives an ICU-specific information program on the day before surgery.

### Inclusion and exclusion criteria

The study is conducted in cooperation with the Department of Heart Surgery and the Department of Visceral, Thoracic and Vascular Surgery at the University Hospital Gieβen and Marburg, Location Marburg, Germany. In principle, all patients of these surgical departments that await elective surgery with a planned subsequent admission to the intensive care unit are eligible for this study. Mainly patients that undergo coronary artery bypass surgery and valve replacement or high risk patients undergoing thoracotomy, gastrectomy, pancreatic surgery, laparatomy, and rectal extirpation fulfil these criteria. In addition, all patients must be over 18 years of age, fluent German speakers and capable of filling out questionnaires. Further exclusion criteria are: pregnancy, not able to complete a questionnaire, the inclusion in another ongoing clinical trial or submission to a surgical ICU within the last year (this latter criteria renders the impact of an information program less likely).

### Randomization

A block-wise balanced randomization procedure will be used. The allocation to either the intervention or the control group can be found on cards that are sealed into opaque and consecutively numbered envelopes. These envelopes will be opened after the patient has finished the baseline questionnaire. Type of surgical department (heart surgery or visceral, thoracic, vascular surgery) is the only stratification factor and separate piles of envelopes will be prepared for these two groups of patients.

### Blinding of participants

Because of the obvious nature of the intervention patients and field researchers cannot be blinded. Data entry and analysis will be conducted by a neutral researcher who was not involved in data acquisition. Group allocation will be concealed to the analyst until the final analysis of the defined primary and secondary outcomes.

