### Development of the information program

In developing the ICU-specific information program, two main criteria were taken into account: comprehensibility and congruency to informational needs. In addition, empirical and theory based recommendations for patient information were considered [21]. Comprehensibility and congruency were accomplished by using the results of the preliminary studies, additional field observations and informal interviews on the involved wards and finally research literature on the experience of ICU-patients [3,22-32].

A pretest of the program then was carried out to further adapt and fine-tune it. This was done on N = 22 patients with elective ICU-stay [33].

The final program consists of two parts with procedural, sensorial and coping information specifically referring to the ICU-stay (Table 2). The first part is laid down as a standardized text; the verbal information is supplemented by two pictures showing relevant elements of the correspondent ICU. The second part of the program consists of seven cards that show the seven top rated fears associated with ICU-stay as they were named in the pretest. On the backside of the cards are short descriptions of what is done on ICU to counter the feared dangers.

Patients may choose cards that represent their fears and are then presented the fear-rebutting information on the back of the respective card. Furthermore, patients have the opportunity to ask additional open questions. The information program will take about 15 minutes and is given on the day before the scheduled surgery. The intervention is performed by one of the 2 researchers (each with diploma of Nursing and Health science and a registered nurse), who are not involved in the process of daily patient care.

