#### 2. Observer-rated measures

Postoperative confusion will be monitored on 1^st ^to 3^rd ^postoperative day using the Confusion Assessment Method for the ICU (CAM-ICU) [45,46]. This period was chosen as study results indicate the highest prevalence of postoperative confusion for cardiac surgery patients at these days [47,48]. This instrument is also applicable for mechanically ventilated patients and contains both cognitive and process-related elements. It covers the Richmond Agitation and Sedation Scale (RASS) [49] and 4 delirium characteristics: ,acute onset', ,inattention', ,disorganized thinking' und ,altered level of consciousness'.

As basic trial documentation pre- and post-surgical therapy data is recorded like length of stay, mode of discharge and complications. The Therapeutic Intervention Scoring System (TISS) [50] and the Acute Physiology and Chronic Health Evaluation II (APACHE II) [51] are documented at ICU admission and ICU discharge.

To quantify postoperative recovery the McPeek Recovery Score [52] will be calculated at the end of hospital stay.

Table 1 shows the timetable of the measures during the trial according to the case report form.

Self-rated measures were compiled according to the Total Design Method [53,54] in order to achieve a high degree of study compliance. In addition, a cognitive pretest was executed (N = 3) [55] to verify the properties of the questionnaires by oral interviews. Consequently, the study documentation and the questionnaires were adapted and in the pilot phase of the study a final standard-pretest (N = 5) was done to test responsiveness and feasibility.

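### The reason given for not blinding field researchers does not extend to whoever later rates CAM-ICU, so the confusion outcome is left without a planned rater unaware of arm

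*Protocol article*

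**What the plan says.** All statements are in the protocol article.

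- **Blinding of participants:** "Because of the obvious nature of the intervention patients and field researchers cannot be blinded". Two safeguards follow: "Data entry and analysis will be conducted by a neutral researcher who was not involved in data acquisition", and "Group allocation will be concealed to the analyst until the final analysis of the defined primary and secondary outcomes".
- **Development of the information program:** "The information program will take about 15 minutes and is given on the day before the scheduled surgery". On staffing: "The intervention is performed by one of the 2 researchers"; these two are described as people "who are not involved in the process of daily patient care".
- **Measures, 2. Observer-rated measures:** "Postoperative confusion will be monitored on" postoperative days 1 to 3, "using the Confusion Assessment Method for the ICU (CAM-ICU"). The rater is not named.
- **Outcomes and Data analysis:** confusion within the first three postoperative days heads the list of secondary outcomes, and secondary outcomes are to be tested.
- **Randomization:** the envelope is opened once the patient has completed the baseline questionnaire. Who opens it is not stated.
- **Ethical considerations:** the allocation list is open to the personnel who carry out the study.

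**The concern.** The article treats everyone in the field as one group and declares that group impossible to blind. Delivering the programme and assessing the outcome are separate tasks on different days, and the stated reason covers only the first. With two researchers, one per patient delivering, the tasks can in principle be separated.

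Concealing allocation from the analyst does not make up for this. If a rater who knows the arm records confusion differently in the two arms, the bias is already in the data that the analyst receives. At stake is the interpretation of the confusion result: a difference favouring the programme could not be told apart from a difference in how it was recorded.

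**Working it through.** **Step 1. Does the stated reason cover each role?** The reason is the obvious nature of the intervention.

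| Role | When | Does the reason apply? |
|---|---|---|
| Patient | Day before surgery onward | Yes |
| Person who opens the envelope | After the baseline questionnaire | Yes, through seeing the card |
| Person who delivers the programme | Day before surgery, about 15 minutes | Yes |
| CAM-ICU rater | Postoperative days 1 to 3 | No, unless the same person, or informed by the list or the patient |
| Data entry and analysis | After data acquisition | Not applied; allocation is concealed from the analyst |

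The article describes no programme material that stays with the patient on the ICU. Awareness in the rater would have to come from having delivered the talk, from the envelope, from the allocation list, or from the patient. The first three can be controlled by assigning tasks; the fourth can be reduced and recorded.

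**Step 2. Who acquires the data?** The article does not say. It describes the person for data entry and analysis as outside data acquisition, and gives no such separation for anyone else. The natural inference is that field staff, declared unblinded, acquire the data. No section provides for a CAM-ICU rater unaware of arm.

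**Step 3. Illustration of size.** The article gives no confusion incidence and no figure for rating error, so there is no planned figure to reproduce. Assume:

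- equal true incidence p in both arms, 25% to 40%;
- a share m of true cases, 10% to 20%, unrecorded in the intervention arm only;
- 60 per arm (Data analysis);
- a two-sided 5% test of two proportions, normal approximation.

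Spurious risk difference: d = p × m.

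- Lowest: 0.25 × 0.10 = 0.025, or 2.5 percentage points.
- Highest: 0.40 × 0.20 = 0.08, or 8 percentage points.

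Probability of a significant result with no true effect, where q = p(1 − m), p̄ = (p + q)/2, s0 = √[2p̄(1 − p̄)/60] and s1 = √{[p(1 − p) + q(1 − q)]/60}:

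Φ[(d − 1.96·s0)/s1] + Φ[(−d − 1.96·s0)/s1]

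For p = 0.40 and m = 0.20: q = 0.32, p̄ = 0.36, s0 = 0.0876, s1 = 0.0873. The terms are Φ(−1.051) = 0.147 and Φ(−2.883) = 0.002, which sum to 0.149.

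| Incidence p | Missed share m | Spurious difference (points) | False-positive rate |
|---|---|---|---|
| 25% | 10% | 2.5 | 6.2% |
| 25% | 20% | 5.0 | 10.0% |
| 40% | 10% | 4.0 | 7.3% |
| 40% | 20% | 8.0 | 14.9% |

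The table shows what follows if raters behave as assumed. It is not evidence that they would.

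**The case against.** The strongest defence is that the trial is openly declared non-blinded, that the text contradicts nothing, and that a condensed article need not list who rates what. The study-procedure figure and the measures timetable are not available here, and the full protocol may name the raters. This stands in part: silence about the rater is not itself a fault. What remains is a positive statement that field researchers cannot be blinded, with a reason that does not reach a later rater.

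Four stronger readings are tempting and are not supported:

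- **That the researchers who give the talk also rate CAM-ICU.** The article never says so. That unblinded field staff acquire the data is an inference from one contrast in the blinding section.
- **That the primary outcome is compromised in a way this change would cure.** CINT is filled in by a patient who knows the arm, whoever hands over the form. A separate administrator removes only the provider's influence, and the gain is small.
- **That complications and the McPeek score are affected too.** Nothing in the article shows that these depend on the recorder's expectation.
- **That 2.5 to 8 points estimates the bias.** Incidence, missed share and direction are all assumed. With 10% missed, the false-positive rate rises only to about 6-7%. How far the CAM-ICU features depend on judgement is also not stated; the article says only that the measure is observer-rated.

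Feasibility is a fair objection as well. Two researchers, recruitment of up to one patient per day in each of two departments, and ratings on three postoperative days make complete separation hard to guarantee. This stands, and is why the proposal is conditional on the rota.

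**Conclusion.** The point holds in limited form. The reason given justifies leaving patients and the person who allocates and delivers unblinded; it does not justify declaring every field researcher unblindable. The observer-rated confusion outcome is thereby left open to assessment bias, and concealment at analysis cannot remove it. The size is unknown; 2.5 to 8 percentage points is an illustration under the assumptions listed above. The conclusion rests on the inference that field staff acquire the data and on the absence of any stated provision for a rater unaware of arm. It concerns one secondary outcome. It is a cheap improvement of low to moderate severity, not an error that invalidates the design.

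**What to change.** Reword Blinding of participants along these lines:

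*Patients, and the researcher who opens the envelope and delivers the programme, are not blinded. As far as the duty rota allows, CAM-ICU is rated by the other researcher, who has no access to the envelope or to the allocation list for that patient. Patients are asked not to disclose their group. The rater records any awareness of group. Where feasible, the same researcher hands out the post-ICU questionnaire.*

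Bring two other sections into line: Randomization (the rater is kept away from the envelope) and Ethical considerations (list access excludes the rater for that patient). The questionnaire sentence should not be presented as blinding the primary outcome, since the patient still knows the arm.

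**Cost:** the change uses the existing two researchers and leaves sample size, outcomes and treatment unchanged. It brings scheduling constraints, some ratings may still fall to the delivering researcher, and some patients will reveal their group. The recorded awareness would let the report state how often the rater knew the arm.

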### Study procedure for the individual patient

The study procedure is designed to be compatible with the highly standardized therapy regime of cardiac surgery patients. The single sequences of surgery schedule, surgery, admission on ICU, admission for standard care and discharge are executed due to hospital specific processes (Figure 1). Determination of points of measurement was done according to compiled data of cardiac surgery patients in the Marburg hospital. Patient recruitment is limited to 1 patient per day and department. By the use of a concealed randomized selection procedure with daily assigned random numbers a representative recruiting can be assured.

**Figure 1 F1:**
[figure not shown]
Study procedures for the individual patient.

### Development of the information program

In developing the ICU-specific information program, two main criteria were taken into account: comprehensibility and congruency to informational needs. In addition, empirical and theory based recommendations for patient information were considered [21]. Comprehensibility and congruency were accomplished by using the results of the preliminary studies, additional field observations and informal interviews on the involved wards and finally research literature on the experience of ICU-patients [3,22-32].

A pretest of the program then was carried out to further adapt and fine-tune it. This was done on N = 22 patients with elective ICU-stay [33].

The final program consists of two parts with procedural, sensorial and coping information specifically referring to the ICU-stay (Table 2). The first part is laid down as a standardized text; the verbal information is supplemented by two pictures showing relevant elements of the correspondent ICU. The second part of the program consists of seven cards that show the seven top rated fears associated with ICU-stay as they were named in the pretest. On the backside of the cards are short descriptions of what is done on ICU to counter the feared dangers.

Patients may choose cards that represent their fears and are then presented the fear-rebutting information on the back of the respective card. Furthermore, patients have the opportunity to ask additional open questions. The information program will take about 15 minutes and is given on the day before the scheduled surgery. The intervention is performed by one of the 2 researchers (each with diploma of Nursing and Health science and a registered nurse), who are not involved in the process of daily patient care.

### Measures

#### 1. Self-rated measures

The current emotional patient state is measured with the state-part of the German version of the State-Trait-Anxiety-Inventory (STAI) [34] after readmission to standard care (post-ICU) and 3 months after discharge. At the point of readmission to standard care unit, ICU-related experiences are assessed using the CINT, a scale specifically developed for these purposes and used in preliminary studies of our working group [4,35,36].

Furthermore, health-related quality of life is measured using SF-12 [37] at baseline and 3 months after discharge. Also 3 months post-discharge patient satisfaction is measured using selected items from the Lübecker-Fragebogen-Doppelkarte [38]. Further baseline characteristics that are relevant to our research questions and distinguish between different types of patients are: Trait-Anxiety-Scale [34], preoperative need for information with the Amsterdam Preoperative Anxiety and Information Scale (APAIS) [39], a modified version of the Need-for-Cognition-Scale (NC) [40-43] to measure individual differences in cognitive preoccupation, and finally subjective illness conceptions using assorted items of the Aachener Fragebogen zur Krankheitsattribution (AFKA_I) [44].

#### 2. Observer-rated measures

Postoperative confusion will be monitored on 1^st ^to 3^rd ^postoperative day using the Confusion Assessment Method for the ICU (CAM-ICU) [45,46]. This period was chosen as study results indicate the highest prevalence of postoperative confusion for cardiac surgery patients at these days [47,48]. This instrument is also applicable for mechanically ventilated patients and contains both cognitive and process-related elements. It covers the Richmond Agitation and Sedation Scale (RASS) [49] and 4 delirium characteristics: ,acute onset', ,inattention', ,disorganized thinking' und ,altered level of consciousness'.

As basic trial documentation pre- and post-surgical therapy data is recorded like length of stay, mode of discharge and complications. The Therapeutic Intervention Scoring System (TISS) [50] and the Acute Physiology and Chronic Health Evaluation II (APACHE II) [51] are documented at ICU admission and ICU discharge.

To quantify postoperative recovery the McPeek Recovery Score [52] will be calculated at the end of hospital stay.

Table 1 shows the timetable of the measures during the trial according to the case report form.

Self-rated measures were compiled according to the Total Design Method [53,54] in order to achieve a high degree of study compliance. In addition, a cognitive pretest was executed (N = 3) [55] to verify the properties of the questionnaires by oral interviews. Consequently, the study documentation and the questionnaires were adapted and in the pilot phase of the study a final standard-pretest (N = 5) was done to test responsiveness and feasibility.

